#### Control arm

Representing treatment as usual, the intervention is delivered in accordance with the BA protocol [17], the IAPT service delivery protocol [37], accredited training received during their PWP training programme [38], and the one day training delivered by the research team to introduce the intervention and case studies in the written self-help format developed for the study.

#### Intervention arm

The written BAcPAc self-help intervention is identical to the self-help intervention used in the control arm with the exception of the following adaptations made to include targeted PA promotion elements (Figure 2).

**Figure 2 F2:**
[figure not shown]
Intervention processes.

i) The rationale for the intervention is altered to emphasise and reinforce the added value of activities that include a PA component.

ii) Principles derived from self-determination theory [24,26] are used to inform the development of the BAcPAc self-help intervention. In particular, this was used to adapt the text and content of the support provided by the PWP to help motivate and engage participants to maintain and develop plans to initiate more activities that involve sustainable PA into their normal weekly planning.

iii) If the PWP identifies participant mood starting to improve during treatment he/she encourages the participant to further increase PA using principles informed by self-determination theory [24] alongside techniques derived from motivational interviewing [42]. This helps maintain participant motivation to continue with the PA identified as part of the standard BA aspect of the intervention.

iv) The diary keeping elements of the BAcPAc self-help intervention were adapted to specifically prompt the participant to continue to monitor and plan their PA using the worksheets included within the intervention.

v) On occasions when the participant has planned PA involving walking within their diary, the PWP encourages the participant to use a pedometer [43] and record the number of steps taken per day on the appropriate worksheets included within the BAcPAc self-help intervention.

vi) Finally, unlike participants in the control arm, those randomised to the BAcPAc arm receive a 10–15 minute follow-up phone call by the PWP one month after the end of treatment at a time agreed between the PWP and participant during the last support session. The aim of this appointment is to review progress with the BAcPAc self-help intervention and support the participant to continue with PA by encouraging them to continue to self-monitor PA using diaries and/or pedometers, problem-solve any difficulties, and resume the BAcPAc self-help intervention and case studies if they identify any worsening of mood.

### Blinding

Participants and research staff conducting assessments are kept blind to study arm allocation as far as possible. Throughout duration of the trial, participants are reminded not to disclose the study arm they have been randomised to during contact with the researcher. A member of the research team collects research data, with blinding concerning participant study arm allocation maintained as far as possible. A researcher (CP) checks all data for accuracy before conversion to electronic format using TeleForm software (http://www.cardiff-teleform.com). Cardiff TeleForm is programmed to perform a range checks for numerical data and to inspect every data entry point is present. All data collected from participants will be assigned a unique ID number and kept separate to any patient identifiable data. All data is kept in lockable cabinets at the University of Exeter, and is not shared with anyone outside the research team. Statistical analyses are undertaken by a member of the research team (FW) blinded to study arm allocation. Instances that arise regarding accidental disclosure of allocation are recorded by the unblinded research team member.

### Outcome measurement

#### Feasibility outcomes

The feasibility outcomes are related to the aims associated with a pilot RCT [44]. Descriptive comparisons across the primary outcome measures of interest will be made between the two recruitment sites adopting different recruitment techniques. The feasibility outcomes are outlined in Table 1.

#### Assessments

To inform inclusion within a definitive phase III RCT, data on the following assessments will be collected.

i. Diagnosis of depression: ICD-10 diagnosis as a binary (yes or no) outcome by the CIS-R [32].

ii. Symptoms of depression and index of depressive relapse: PHQ-9 [35] based upon an adapted protocol [45].

iii. PA sedentary behaviour and total energy expenditure: assessed using an accelerometer (GENEActiv) worn on the wrist for one week and a 7-day PA recall survey [46].

iv. The Insomnia Severity Index (ISI) [47].

v. Health-related quality of life: Short Form-36 (SF-36 [48]) and EuroQol (EQ-5DL [49]).

vi. Health and social care services use and cost: simplified version of the Adult Service Use Schedule (ADSUS [50]).

vii. Blood pressure: the average of the last two from three measurements taken seated from the left arm following 10 minutes of rest measured using an Omron M7 Monitor.

viii. Body mass index: weight measured using Omron HN286 Digital Scales and height measured using a tape measure.

In addition, general demographic information, including gender, age, ethnicity, marital status, smoking status, postcode, number of dependants, and age of leaving education, is collected from all participants at baseline.

### Data collection

The researcher collects general demographic information during telephone screening. All other data informing the feasibility outcomes is extracted from routine service records by the PWP delivering the intervention at the end of the support session, by the researcher during 4-, 9-, and 12-month follow-up, or from process interviews. All participants will be followed-up despite any deviation from planned treatment. Time points representing collection of the assessments are highlighted in Table 2.

**Table 2 T2:** Assessments administered at screening, baseline, and follow-up post-baseline

	**Screening**	**Baseline**	**4 months post baseline**	**9 months post baseline**	**12 months post baseline**
PHQ-9	X		X	X	X
CIS-R	X		X	X	
Physical activity					
7 day PA recall		X	X		
Accelerometer			X	X	
Body mass index		X	X	X	
Blood pressure		X	X	X	
Health and social care service use (ADSUS)		X	X	X	
Sleep-insomnia severity index		X	X	X	
Quality of life					
SF-36		X	X	X	
EQ-5D		X	X	X	

Assessments taken at baseline are collected face-to-face or over the telephone depending upon patient preference, with height, weight, and blood pressure collected face-to-face. All data collected at 4-month follow-up is collected face-to-face, with 9 and 12 month follow-up data collected face-to-face or over the phone, depending on patient preference. Adverse events are reported by PWPs to the researcher during routine communication and spontaneously. The researcher inquires of any adverse events at follow-up. Any events are recorded and escalated to the PI, and if necessary, to the sponsor.

### Process evaluation

The aims of the process evaluation are to assess or identify: i) the acceptability of the BAcPAc intervention for patients and PWPs, ii) the fidelity of delivery of the BAcPAc intervention (how well does delivery match our intentions), iii) additional training needs for PWPs delivering the interventions, iv) any future adaptations needed in the BAcPAc intervention. Data gathered as part of the process evaluation will be used to further adapt the BAcPAc written self-help intervention and training in preparation for the phase III RCT. Qualitative interviews are conducted with participants randomised to the BAcPAc study arm and with PWPs supporting the interventions.

#### Qualitative interviews

After the final support session, all participants receiving the BAcPAc intervention are invited to participate in a semi-structured interview. This examines intervention acceptability and identifies adaptations that participants feel may improve the assessment or support provided for the BAcPAc intervention. Interviews follow a predetermined interview schedule, with the topic guide (Additional file 5) partially informed by a previous qualitative study investigating acceptability of CBT self-help for the treatment of depression in patients with chronic physical illness [51]. This was developed in consultation with the intervention development team and a patient and public involvement group specifically established to support the study. Interviews are digitally recorded and transcribed verbatim. Data is analysed using framework analysis [52] alongside constant comparison techniques [53] to generate concepts and themes. To ensure rigour, the researcher reads transcripts and develops the initial categorisation, with second coding undertaken by another member of the research team. Further categorisations are discussed amongst the team and amendments to categories and definitions made as required [54]. Qualitative data is analysed using ‘surface level’ thematic analysis only. This involves coding the data to extract concepts and grouping the concepts together into themes.

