### Study design

This study employs a single (researcher) blind, parallel-randomised controlled trial design with nested mixed methods process evaluation. Subjects are randomised individually in a 1:1 ratio to either a written self-help intervention based upon BA combined with PA promotion (BAcPAc) or a written self-help intervention based upon BA alone, representing treatment as usual (TAU) (Figure 1) [34].

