### Randomisation

A web-based minimisation service supported by the Peninsula Clinical Trials Unit ensures concealment allocation of participants to a PWP who has either been trained to deliver BA as usual or BAcPAc. To preserve researcher blinding regarding the study arm participants are randomised into, the Peninsula Clinical Trials Unit sends an e-mail containing randomisation details for the participant to the IAPT service administrator and a PWP supporting the intervention within that service. At the same time, the participant’s ID number with no other personal information is also e-mailed to the researcher.

Minimisation is based on the following prognostic factors: participant age (10–30 years or >31years), sex (male or female), PHQ-9 [35] score (moderate/moderately-severe 10–18; moderately-severe/severe 19–23), current use of anti-depressant medication (yes or no), and recruitment site (Plymouth or East and Mid Devon). To maintain concealment, the minimisation algorithm retains a stochastic element, providing a degree of unpredictability during the allocation process. The first participant was randomised on the 23^rd^ of April 2013.

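### The role kept blind for outcome assessment also codes the BAcPAc-only interviews and receives the PWPs' adverse-event reports, with no stated safeguard

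*Protocol article*

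**What the plan says.** On blinding, the Study design section reads: "This study employs a single (researcher) blind, parallel-randomised controlled trial design". The Randomisation section sends allocation details to the service administrator and a PWP, with the purpose given as "To preserve researcher blinding regarding the study arm participants are randomised into"; for each randomisation, "the participant’s ID number with no other personal information is also e-mailed to the researcher". The Blinding section adds: "Participants and research staff conducting assessments are kept blind to study arm allocation as far as possible". It also blinds the analyst, and it mentions an unblinded team member whose only stated task is to log accidental disclosures.

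On tasks, the Data collection section has the researcher collect the follow-up data at 4, 9 and 12 months. It also states: "Adverse events are reported by PWPs to the researcher during routine communication and spontaneously". Under Treatments, the PWPs at both sites are randomised so that two deliver BAcPAc and two deliver BA alone.

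On the interviews, the Process evaluation section states: "Qualitative interviews are conducted with participants randomised to the BAcPAc study arm and with PWPs supporting the interventions". All BAcPAc participants are invited once their last support session is over. For the analysis, "the researcher reads transcripts and develops the initial categorisation, with second coding undertaken by another member of the research team".

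**The concern.** The allocation e-mail is routed around the researcher to protect the blind. Later sections then give the same named role two streams of information that can reveal allocation. A participant transcript exists only if that person was in BAcPAc, so knowing whose transcript it is means knowing the arm. An adverse-event report comes from a PWP who works in one arm only.

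What is at stake is the follow-up data that this role collects from participants. Table 1, item 4, uses the between-arm difference in CIS-R diagnoses to inform the phase III sample size. An assessor who knows which participants had BAcPAc could influence that difference. The pilot is also meant to try out trial methods, and assessor blinding is one of them.

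**Working it through.** **The plan's own figure.** The Sample size section gives 40 per arm, from about 30 per arm and 20% attrition. 30 / (1 − 0.20) = 37.5, so 38; working back, 40 × 0.80 = 32, which fits about 30. The figure is taken as stated, and the point does not depend on it.

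**Step 1: who holds which task.**

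| Section | Task | Named holder |
|---|---|---|
| Randomisation | Kept blind, receives ID only | the researcher |
| Screening, baseline, and informed consent | Baseline CIS-R | the researcher |
| Data collection | 4-, 9- and 12-month data | the researcher |
| Data collection | Receives PWP adverse-event reports | the researcher |
| Qualitative interviews | Reads transcripts, first coding | the researcher |
| Qualitative interviews | Second coding | another team member |
| Intervention fidelity checking | Listens to recordings | a team member |
| Blinding | Logs accidental disclosures | the unblinded team member |

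The article uses a different term where it means someone else. The natural reading is that the transcript reader and the outcome assessor are the same role.

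**Step 2: timing.** The Abstract caps treatment at 4 months, and the interview invitation follows the last support session. Interviews therefore normally fall before the 9- and 12-month assessments. No date is given for coding. Table 2 marks the CIS-R at 4 and 9 months and the PHQ-9 at 4, 9 and 12. The Abstract lists the CIS-R among measures at 4, 9 and 12 months. The outcomes exposed are thus the CIS-R and PHQ-9 at 9 months, the PHQ-9 at 12 months, and the CIS-R at 12 months only if the Abstract is right.

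**Step 3: does the unique ID protect?** The Blinding section replaces identifiers with an ID. The researcher is e-mailed that ID at randomisation and, under Confidentiality, is the only holder of the key to the paper personal data. A transcript carrying the ID can be linked to its participant. Full anonymisation or delayed access would protect, but neither is stated.

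**Step 4: adverse events.** A report reveals the arm if the researcher knows which arm the PWP delivers, or if the report discloses it. The article says neither. PWPs are interviewed too, so if the researcher also reads their transcripts, their arms could become known that way.

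**Step 5: size of the transcript route.** Uptake u is not given and is an assumption. With 40 per arm, attrition ignored, and transcripts that are linkable and read before follow-up ends:

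- allocations known = 40u
- share of all participants = 40u / 80
- share guessed correctly if everyone else is assumed to be in BA alone = (40u + 40) / 80, against 50% by chance

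| u | Known | Share of 80 | Correct guesses |
|---|---|---|---|
| 25% | 10 | 12.5% | 62.5% |
| 50% | 20 | 25% | 75% |
| 75% | 30 | 37.5% | 87.5% |
| 100% | 40 | 50% | 100% |

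If transcripts are anonymised, or read after the last follow-up, exposure by this route is close to nil.

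**Step 6: participant blinding.** Study design claims researcher blinding only. The Blinding section says participants are blind as well, and its next sentence has them reminded not to reveal their arm, which presumes that they know it. Under Treatments they are introduced to the material for their own arm.

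**The case against.** A reader might infer that the plan breaks its own blind. The documents do not go that far, because three premises are unstated: that one person fills every task assigned to the researcher, that coding starts before the last follow-up, and that transcripts can be linked to participants. The Blinding section shows several people at work, including an unblinded one, and attributes data collection to a member of the team. The article does not say who conducts the interviews. Table 1 places them loosely after participation. A condensed article may leave such staffing detail to the full protocol. This stands against the word broken. It does not remove the conflict in the printed text, which assigns arm-revealing work to the role it says is blind.

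A reader might also infer that every adverse-event report from a PWP discloses the arm. That needs the researcher to know each PWP's arm, which is nowhere stated.

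Blinding is promised only as far as possible, and accidental disclosures are logged. So it would be too strong to say that the pilot can teach nothing about blinding. But that qualifier covers disclosures that cannot be avoided. It does not justify handing the assessor material from one arm.

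Finally, this is a pilot with no hypothesis test and no primary outcome, and most feasibility outcomes in Table 1 do not depend on a blinded assessor. That stands, and it lowers the weight of the point.

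**Conclusion.** The point holds as an exposure without a stated safeguard. Followed as written, the plan gives the role that is kept blind and collects follow-up outcomes both the first coding of BAcPAc-only participant interviews and the adverse-event reports of single-arm PWPs. The outcomes at risk are those collected after the interviews, as set out in Step 2.

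The number of allocations exposed runs from close to none to all 40 in BAcPAc. It depends on uptake, on whether transcripts are linkable and on when they are read, none of which is given. The adverse-event route adds to this only if the PWPs' arms are known to the researcher.

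Severity is moderate. The main use affected is the CIS-R difference in Table 1, item 4. The statement on participant blinding is a separate, minor contradiction that needs no assumption.

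**What to change.** 1. Assign first coding to the unblinded team member already mentioned under Blinding, or to the existing second coder if that person does no outcome assessments. Alternatively, withhold transcripts from the outcome assessor until the last 12-month assessment is done. State who conducts the interviews, and keep that person separate from outcome assessment too.
2. Route PWP adverse-event reports to the unblinded member. The onward escalation described under Data collection can stay as it is.
3. Amend the Blinding section so that it no longer says participants are blind, in line with Study design.
4. State which of the Abstract and Table 2 is right on the 12-month CIS-R, so that it is clear which assessments need protecting.

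The article reports 60 patients already recruited, so the trial report should also say who coded the transcripts and when.

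The cost is reassigned work among existing team members, or qualitative coding that starts later and so informs intervention refinement later. No new visits are needed.

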#### Intervention fidelity checking

All support sessions (face-to-face or telephone) in both study arms are digitally recorded. A 20% sample is then assessed to review intervention fidelity for each PWP using an intervention fidelity measure. Recordings are listened to by a member of the research team, who applies the intervention fidelity measure to rate competence in each element of the intervention. Based on previously used intervention fidelity measures [26,55] and informed by a prior intervention mapping procedure [56], a version specifically developed for the BAcPAc intervention (Additional file 6) was adopted. The measure incorporates the Dreyfus skill acquisition scale [57] to rate the competence of providers in delivering the targeted techniques and delivery processes. The scale produces a score of 0 to 6 for each targeted element of the intervention process and is anchored so that a score of 3 is considered acceptable, 0 is non-existent, and 6 is perfect performance. Intervention fidelity measure scores are summarised using simple descriptive statistics (means and standard deviations) and collated both in total and by therapist. Examples of good practice are flagged, transcribed, and extracted as audio clips or text transcripts to inform future training. Items scoring low for some or all PWPs supporting the intervention are used to identify areas where change is needed to the intervention materials or PWP training course.

### Statistical analysis

#### Quantitative

For both recruitment settings, participant flow will be summarised using the CONSORT flow diagram adapted for complex interventions [58], reporting recruitment and attrition rates (both treatment and study drop-outs) with 95% confidence intervals. The CONSORT flow diagram will also be adapted to reflect the number of recruitment letters sent, numbers consenting, number randomised, number undertaking intervention, and number of completed outcomes alongside means, standard deviations and frequencies regarding the number of support sessions, session length, and mean number of days between support sessions. All protocol deviations, along with number of missing items on questionnaires, will be reported. Mean and standard deviations for general demographic information will be reported at baseline with assessments conducted at baseline and 4-, 9-, and 12-month follow-up.

#### Economic analysis

Factors related to collecting self-reported data on participant NHS and related resource use will be examined. Informed by case report forms, methods for estimating the resource use and costs associated with delivery of the intervention will be developed and tested. Whilst it is not possible to estimate cost-effectiveness in this pilot study, estimates of intervention cost will inform exploratory modelling and estimates of the resources and costs needed to run a future trial. In a future phase III RCT, cost-effectiveness analysis is expected to involve both within-trial analysis and evidence synthesis with decision-analytic modelling, to assess the longer-term consequences of the intervention (e.g., changes in outcomes, events avoided, life-years, and quality-adjusted life-years gained). It is expected that this modelling will use/adapt existing economic models on outcomes for depression and PA promotion, and the subsequent cost-effectiveness of interventions. This study will be used to conduct preliminary investigations on how best to construct such analyses and develop an economic evaluation plan for the planned phase III RCT. A summary of the results will be available to participants who have requested this during consent, and a report provided to the participating IAPT services. The findings will be reported in a number of peer reviewed journals.

### Ethical approval

This protocol has been reviewed and approved (26/03/2013) by the NHS South West Regional Ethics Committee (REC reference number: REC/SW/0291).

### Changes to methods since recruitment began

Since trial recruitment began in April 8^th^ 2013, the following important changes have been made:

1) A small number of potential participants from Mid and East Devon had reported that they would experience difficulties taking part in the study if they could not be seen at a convenient location. Originally, PWPs were only seeing participants in one location. We therefore extended the number of locations where patients could be seen for treatment and, as the service routinely offer face-to-face or phone appointments to patients, we also changed the information sheet to emphasise that participants entering the study could be treated either face-to-face or over the phone. (Approved 15/08/2013)

2) Participants often have had their prescription changed by their GP at the same time as referral to the service, and so we were excluding many potential participants. This has been considered useful for previous trials to establish stability in mood prior collecting baseline measures, but is not a clinical requirement. Given a high rate of exclusion from this study, we are now recording if participants have changed or been prescribed an antidepressant in the last month, and are collecting information about current and past medication from all participants at baseline and follow-up. We have therefore removed the exclusion criteria “changed or newly prescribed antidepressant in the previous month”. (Approved 15/08/13)

